
### Outcomes

Primary Endpoint3-year disease-free survival (DFS): Time from patient randomization to disease progression/death.Secondary EndpointOverall survival (OS): Time from randomization to death from any cause.Quality of life (QoL): The patient’s quality of life, including the living conditions of patients (EORTC QLQ-C30/CX24).Perioperative clinical dataOperation timeIntraoperative blood lossPelvic lymphocyst/Lymphedema of lower limb/Edema of vulva/ Deep venous thrombosis (DVT)/fever (T ≥ 37.5℃)/Postoperative hospital stay.Sentinel lymph node dataIdentified time of SLNIdentified ratio of SLNIdentified site of SLNNegative predictive value of SLNFalse negative rate of SLN

### Postoperative adjuvant therapy

This study will assess whether patients need postoperative adjuvant therapy according to National Comprehensive Cancer Network (NCCN) guidelines. The implementation and management of radiotherapy will be carried out according to clinical practice guidelines. Researchers are required to record the dose and start and end time of radiotherapy or concurrent chemoradiotherapy. Isolated tumor cells and micrometastasis can be considered as positive lymph nodes, but they have no impact on the adjuvant treatment of patients. We don’t plan to use molecular typing to guide adjuvant treatment planning since research on adjuvant therapies incorporating molecular classification are currently ongoing and not yet well established by high-level prospective RCT research data, such as RAINBOW, PROTEC IVA, etc. According to the NCCN guidelines, the radiotherapy doctors in the research team develop an adjuvant therapy plan, which is then reviewed by the PI of the sub center, and periodically reviewed by the main PI.

### Qualification certification for participating physicians

The surgeons participating in the operations must be qualified gynecological oncologists and have records to prove that they can well complete minimally invasive TH + BSO + PL ± paraaortic lymph node resection. To minimize the surgical complications of surgeons in the initial learning stage, gynecological oncologists participating in the study must have finished laparoscopy in more than 50 cases of endometrial cancer surgery, with an annual average of 15 cases. Also, laparoscopic ICG fluorescence sentinel lymph node biopsy must have been carried out in more than 30 cases. Also, the trial management committee was provided with non-edited surgical videos from two recent years and the data of 50 surgical patients from three recent years. Case information will be kept confidential to protect the confidentiality of patients. The required information shall include:

AgeBody mass indexStagingOperation timeIntraoperative blood lossLength of stayIntraoperative complicationsPostoperative complications (within 30 days after operation)Blood transfusion volume (intraoperative and postoperative)

The trial management committee will evaluate and judge each surgical video according to the following criteria:

surgeon’s surgical techniquesanatomical cognition and anatomical ability of pelvic structuresurgical techniques to control intraoperative blood loss and prevent intraoperative injuryability to make decisions based on intraoperative explorationaccuracy of relevant instruments used during surgery

Once the chief investigator of each center is recognized, he/she can judge the ability of surgeons in his/her institution to cooperate in the study, to ensure that the above criteria are met.

### Randomization and stratification

The subjects were screened by a random system; a random distribution sequence was generated; and the corresponding surgical treatment will be performed according to the random results. Random stratification, age (≥ 50 years or < 50 years), surgical method (laparoscopic surgery or robotic surgery).

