
## Methods

### Trial design and surgical quality assurance

The INSEC study (ChiCTR1900023161) is a randomized, open-label, multicenter and non-inferiority controlled clinical trial in China. Potential participants will be patients with pathologically confirmed endometrial cancer at the Zhejiang Cancer Hospital, Jiaxing Maternity and Child Health Care Hospital, and the First Hospital of Jiaxing in China. Patients will be randomly assigned in a 1:1 ratio to two groups, Arm A and Arm B (Fig. 1). Patients in Arm A will undergo sentinel lymph node biopsy (SLNB) + total hysterectomy (TH) + bilateral salpingo-oophorectomy (BSO) ± paraaortic lymph node resection. Patients in Arm B will undergo SLNB + TH + BSO + pelvic lymphadenectomy (PL) ± paraaortic lymph node resection.

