### Qualification of surgeons

So far, there is no consensus on whether sentinel lymph node biopsy can replace lymphadenectomy in the treatment of patients with early endometrial cancer. The need for qualification and training of surgeons involved in these studies is particularly important, especially on minimally invasive surgery techniques and cervical ICG injection. The current study asks that surgeons involved in the study have operated on more than 50 cases of endometrial cancer by independent minimally invasive surgery and injected ICG into the cervix in more than 30 cases. In addition, it is suggested that the participating center should be a gynecological oncology center with sufficient patients, and should have sentinel lymph node ultra-staging technology. Then, it will be carefully evaluated in stratification. We look forward to the prognostic data of the study in a few years.

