### Statistical methods

Disease-free survival and overall survival curves will be evaluated using the Kaplan Meier method. The survival difference between the two groups will be analyzed by log-rank method. The analysis of prognostic factors will use appropriate regression models (such as Cox model). Efficacy indicators will be compared through intention-to-treat analysis including all randomized patients. Toxicity will be analyzed based on the treatment received. The 95% confidence interval of the difference between the two groups will be calculated at the same time. Descriptive statistical analysis will be used for treatment-related adverse events and quality of life scores (QLQ-C30, QLQ-CX24). The normality and equality of differences between the two groups of continuous variables will be evaluated. Discrete variables (such as presence/absence of postoperative infection) will be aggregated by frequency/proportion.

For continuous variables, analysis of variance and/or regression analysis will be used as appropriate. If the assumptions of these tests are violated, an alternative nonparametric test method will be used. Differences in discrete variables between groups will be assessed by chi square test. The risk proportional regression model will be used to explore the prognostic factors such as age, degree of differentiation, lymph node metastasis, and PS-ECOG.

The hypothesis H0: “Sentinel lymph node biopsy alone is not inferior to sentinel lymph node biopsy plus lymphadenectomy for early stage endometrial cancer with negative nodal assessment intraoperatively.”

In the current study, there are three patient groups: intention-to-treat (ITT) group, including all randomized patients who signed the consent form; a group of those in serious violation of the protocol, excluded from the efficacy analysis; and a safe population of all randomized patients who at least start the study treatment.

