### Sample size

The primary endpoint of this study is 3-year DFS. According to the results of previous research, patients with stage I endometrial cancer who received laparoscopy had 3-year DFS of 88.6% [18]. It is assumed that the 3-year DFS of the reference group and the experimental group is 88%, and the non-inferior boundary value is 8%. Considering the 20% loss of follow-up rate, 361 subjects need to be included in each group to ensure 80.0% power using a 2-sided log-rank test with a type I error rate of 0.05 to reject the null hypothesis. The total sample size of this study is 722 and the number of outcome events in each group is 40. The sample size calculation was done using the PASS software (version 11.0).

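### The primary comparison is not described as accounting for the randomization factors (age group, surgical method): a valid analysis, with a small efficiency gain available on the 3-year DFS difference

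*Protocol article*

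**What the plan says.** All places are in the protocol article.

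- **Randomization and stratification** lists two factors: "Random stratification, age (≥ 50 years or < 50 years), surgical method (laparoscopic surgery or robotic surgery". That makes 2 × 2 = 4 cells. Centre is not listed.
- **Statistical methods** gives the comparison: "The survival difference between the two groups will be analyzed by log-rank method". It adds: "The 95% confidence interval of the difference between the two groups will be calculated at the same time". Neither sentence says whether the analysis is stratified or adjusted.
- **Statistical methods** gives regression a different purpose: "The risk proportional regression model will be used to explore the prognostic factors such as age, degree of differentiation, lymph node metastasis, and PS-ECOG". Age is among the examples; surgical method and centre are not.
- **Sample size** sets the margin on the difference scale (in percent): "It is assumed that the 3-year DFS of the reference group and the experimental group is 88%, and the non-inferior boundary value is 8". The test is again an unqualified log-rank: "to ensure 80.0% power using a 2-sided log-rank test with a type I error rate of 0.05".
- **Qualification of surgeons**, straight after the requirements for surgeons and centres, says: "Then, it will be carefully evaluated in stratification". What is to be evaluated is not stated.
- **Trial design and surgical quality assurance** names three sites: "Zhejiang Cancer Hospital, Jiaxing Maternity and Child Health Care Hospital, and the First Hospital of Jiaxing in China".

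**The concern.** Stratified randomization balances the arms on the chosen factors. If those factors predict outcome, the treatment estimate varies less than an unadjusted standard error assumes, so an unadjusted interval for the 3-year DFS difference is a little wider than it need be. In a non-inferiority trial that width is paid for in power: the interval must stay inside an 8-point margin, and about 80 events are planned.

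The article brings in covariates only to explore prognosis and names one of its two randomization factors, surgical method, in no analysis. It also mentions stratification next to the surgeon and centre requirements, which the list of factors does not carry through. At stake are some precision, and clarity about which result will be set against the margin if adjusted and unadjusted results differ near it.

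**Working it through.** **1. The plan's own event count.** Inputs from Sample size: 88% 3-year DFS in both arms, margin 8 points, 80% power, 361 per arm, 20% loss, 40 events per arm.

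- Implied hazard-ratio margin: ln(0.80)/ln(0.88) = 1.746, with log 0.557.
- Events = 4(z_α + z_β)²/0.557². With one-sided 0.05: 4(1.645 + 0.842)²/0.310 ≈ 80, which is 40 per arm, as stated.
- With two-sided 0.05, as written, the same formula gives 102 events, and 80 events give about 70% power. That mismatch is a separate matter; here it shows only that there is little power to spare.

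**2. Stratifying the log-rank or Cox analysis.** The article gives neither cell sizes nor prognostic effects. Assumed: 70% aged 50 or over, 20% robotic, centres split 60/20/20, and prognostic hazard ratios for age/method/centre from 1/1/1 to 3/2/2. Simulation with 722 patients, 1,500 runs per setting:

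| Analysis | Mean SE of log hazard ratio | Change in power (95% CI bound) |
|---|---|---|
| Unstratified | 0.2289–0.2316 | reference |
| Two factors (4 cells) | 0.2290–0.2317 | −0.6 to +0.1 points |
| Plus centre (4 × 3 = 12 cells) | 0.2305–0.2337 | −1.0 to −0.2 points |

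Precision here is governed by the number of events. Stratifying does not add any, and many small cells lose a little information.

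**3. Adjusting the 3-year DFS difference.** Evaluable per arm: 361 × 0.8 = 288.8. Unadjusted SE = √(2 × 0.88 × 0.12/288.8) = 0.02704; half-width 1.96 × SE = 5.30 points; power = Φ(0.08/0.02704 − 1.96) = 84.1%. If the factors explain a share R of the outcome variance, the SE is multiplied by √(1 − R). Same assumptions as step 2:

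| Hazard ratios (age/method/centre) | R, two factors | R, plus centre | Half-width, two factors / plus centre | Power, two factors / plus centre |
|---|---|---|---|---|
| 1/1/1 | 0 | 0 | 5.30 / 5.30 | 84.1% / 84.1% |
| 1.5/1.2/1.2 | 0.4% | 0.5% | 5.29 / 5.29 | 84.3% / 84.3% |
| 2/1.5/1.5 | 1.3% | 1.7% | 5.27 / 5.26 | 84.6% / 84.7% |
| 3/2/2 | 3.2% | 4.4% | 5.22 / 5.18 | 85.2% / 85.7% |

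The largest gains are 85.23 − 84.09 = 1.1 points and 85.68 − 84.09 = 1.6 points.

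**4. Validity of the unadjusted test.** If randomization balances the strata, the true one-sided error is 1 − Φ(1.96/√(1 − R)). For the two factors this is 0.025 down to 0.0232. It would reach 0.0225 only if centre were balanced by the randomization too, which the list of factors does not show.

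**5. Grade.** The total variance is 0.88 × 0.12 = 0.1056. Both scenarios are assumed and average 88%.

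- Strong: 75% of patients at 93.3%, 25% at 72%. R = 0.1875 × 0.213²/0.1056 = 8.1%. The half-width falls to about 5.08 points, equivalent to 288.8/(1 − 0.081) − 288.8 ≈ 25 evaluable patients per arm.
- Weak: 80% at 90%, 20% at 80%. R = 0.16 × 0.10²/0.1056 = 1.5%, and the half-width is 5.26 points.

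**The case against.** The strongest reply is that the article is silent rather than wrong. It never calls the log-rank unstratified. A full protocol (version 5.0, under Trial status) exists and an analysis plan may exist, and stratification of a named test is often settled there. This stands: a reader might infer that the trial has decided to ignore its strata, and the text does not support that. What the article does show is that covariates have only an exploratory role and that surgical method is named in no analysis.

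A reader might also infer that the plan gives up precision that could be had for nothing. The figures do not bear this out: stratifying the log-rank gains nothing measurable, and adding centre as strata loses up to about 1 point of power. Only the adjusted DFS difference gains, and modestly.

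The largest figure, 8%, comes from grade, which is not a randomization factor and whose assumed effect is not in the article. Nor does the article say that a curettage grade is recorded for every patient before randomization; it mentions G3 when deciding on paraaortic resection and differentiation as a prognostic factor. That objection stands, so grade belongs in the model only where it is known before randomization.

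Finally, a reader might take chance imbalance between arms as a bias in the primary estimate. It is not: randomization makes such imbalance random, and the confidence interval already allows for it. Nor can the stratification remark under Qualification of surgeons be read firmly as a promise to stratify by centre, because its subject is unclear.

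**Conclusion.** The point holds as a minor one of efficiency and clarity. The randomization factors are not carried into the primary comparison as described, but the unadjusted analysis is valid and errs, if at all, slightly on the conservative side.

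The achievable gain is confined to the 3-year DFS difference: 0 to 3.2% of variance from the two factors, up to 4.4% with centre, and about 1.5 to 8% from grade. All of these rest on assumed cell sizes and prognostic effects. The planned sample size and event count are unaffected. The stratification remark under Qualification of surgeons and the list under Randomization and stratification do not match and need reconciling.

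**What to change.** 1. Base the non-inferiority interval on a 3-year DFS difference that accounts for age group and surgical method, either by stratum-weighted Kaplan-Meier estimates or by standardising from a model. The margin is set in points of 3-year DFS, so this is also the scale it needs.
2. In the model version, adjust also for degree of differentiation where it is recorded before randomization. Do not take over the exploratory model unchanged: it includes lymph node metastasis, and more nodes are removed and examined in Arm B.
3. Report the unadjusted difference as sensitivity, and a log-rank/Cox analysis stratified by the two factors as supportive.
4. Do not add centre as further strata for the log-rank. If centre is used, enter it as a covariate.
5. State under Qualification of surgeons what is to be evaluated in stratification, and make that agree with the listed factors.

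The cost is wording, slightly more analysis work, and the need to fix the model in advance, before outcome data by arm are seen. No additional patients or data are required, given that grade is used only where already recorded.

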### Statistical methods

Disease-free survival and overall survival curves will be evaluated using the Kaplan Meier method. The survival difference between the two groups will be analyzed by log-rank method. The analysis of prognostic factors will use appropriate regression models (such as Cox model). Efficacy indicators will be compared through intention-to-treat analysis including all randomized patients. Toxicity will be analyzed based on the treatment received. The 95% confidence interval of the difference between the two groups will be calculated at the same time. Descriptive statistical analysis will be used for treatment-related adverse events and quality of life scores (QLQ-C30, QLQ-CX24). The normality and equality of differences between the two groups of continuous variables will be evaluated. Discrete variables (such as presence/absence of postoperative infection) will be aggregated by frequency/proportion.

For continuous variables, analysis of variance and/or regression analysis will be used as appropriate. If the assumptions of these tests are violated, an alternative nonparametric test method will be used. Differences in discrete variables between groups will be assessed by chi square test. The risk proportional regression model will be used to explore the prognostic factors such as age, degree of differentiation, lymph node metastasis, and PS-ECOG.

The hypothesis H0: “Sentinel lymph node biopsy alone is not inferior to sentinel lymph node biopsy plus lymphadenectomy for early stage endometrial cancer with negative nodal assessment intraoperatively.”

In the current study, there are three patient groups: intention-to-treat (ITT) group, including all randomized patients who signed the consent form; a group of those in serious violation of the protocol, excluded from the efficacy analysis; and a safe population of all randomized patients who at least start the study treatment.

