So far, there has been no consensus on whether sentinel lymph node biopsy can replace lymphadenectomy in the treatment of patients with early endometrial cancer. The following are the results of sentinel lymph node studies to date. In 2017, Lancet Oncology published the results of robotic sentinel lymph node biopsy (FIRES study) in patients with stage I endometrial cancer. The results showed that the sensitivity of sentinel lymph node biopsy in the diagnosis of lymph node metastasis was 97.2%, and the negative predictive value was 99.6% [10]. Some scholars express concern that sentinel lymph node mapping will miss isolated paraaortic lymph nodes, especially in patients with a high metastasis rate of paraaortic lymph nodes (such as high-grade and tumor-infiltrating deep muscle layer) [11]. To address this concern, Bogani et al. [12] conducted a meta-analysis of the clinical data of 3,536 patients with endometrial cancer who underwent sentinel lymph node biopsy (1,249 cases) or lymphadenectomy (2,287 cases). The results showed that the positive detection rate of pelvic lymph nodes in the sentinel lymph node mapping group was higher than that in the lymphadenectomy group (14.7%: 9.9%). There was no significant difference in the positive detection rate of paraaortic lymph nodes between the two groups. Also, there was no significant difference in the total recurrence rate (4.3%: 7.3%) or lymph node recurrence rate (1.2%: 1.7%) between the sentinel lymph node mapping group and the lymphadenectomy group. In addition, a study found that the sensitivity and negative predictive value of sentinel lymph node biopsy in patients with high-risk histological types of endometrial cancer were 95.0% and 98.6%, respectively. 89% of patients had at least one sentinel lymph node mapping. Of these, 58% were bilateral sentinel lymph nodes, 40% were unilateral sentinel lymph nodes, and 2% were isolated paraaortic lymph nodes [13]. Maria C. Cusimano and Sarah E. Ferguson underwent SENTOR trial and found the acceptable accuracy of sentinel lymph node mapping in high-grade endometrial cancer. Of 27 patients with nodal metastasis, sentinel lymph node mapping correctly identified 26 of them (96% sensitivity; 95% CI; 81%–100%) [14]. A study jointly carried out by Memorial Sloan-Kettering Cancer Center and the Mayo Clinic found that compared with lymphadenectomy, sentinel lymph node biopsy for endometrial cancer with deep myometrial invasion did not affect the tumor outcome, and the prognosis of lymph-node-negative patients was better, but this had nothing to do with the evaluation method of lymph nodes [15]. Sentinel lymph node mapping did not affect the prognosis of high-risk endometrial cancer [16]. Moreover, How et al. [17] systematically evaluated 5,348 patients in 48 studies. The results showed that the total detection rate of SLN detected by ICG combined with near-infrared fluorescence imaging was 94%, which was significantly higher than that by blue staining (86%) and radionuclide method (86%). 34 studies showed a total sensitivity of 94% and a negative prediction rate of 100%. Therefore, indocyanine green combined with near-infrared fluorescence imaging technology has a good clinical application prospect.

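### The only named test (log-rank) carries no margin, so the plan has no stated rule for judging the absolute 8-point margin on 3-year DFS

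*Protocol article*

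**What the plan says.** Under Sample size, the protocol article states that "The primary endpoint of this study is 3-year DFS". The planning assumption follows: "It is assumed that the 3-year DFS of the reference group and the experimental group is 88%, and the non-inferior boundary value is 8" per cent. With 88% in both arms, that reads as an absolute margin of 80% against 88%.

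The same section says "361 subjects need to be included in each group to ensure 80.0% power". It allows for 20% loss to follow-up and gives 40 outcome events per group, 80 in all. The test behind this power is described as "using a 2-sided log-rank test with a type I error rate of 0.05 to reject the null hypothesis".

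Under Statistical methods, survival curves are estimated by Kaplan-Meier, and for the comparison "The survival difference between the two groups will be analyzed by log-rank method". A later sentence, placed directly after the one on toxicity, adds: "The 95% confidence interval of the difference between the two groups will be calculated at the same time". It does not say which difference is meant, and it does not mention the margin. No hazard-ratio bound, margin-shifted test or rule for a confidence limit appears in the article.

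**The concern.** The endpoint and margin are a difference between two proportions at 3 years. The named test compares whole curves against a null of no difference. An ordinary log-rank result cannot settle the question in either direction. A non-significant result may only mean few events, and a significant one does not say whether the loss is under 8 points.

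A log-rank can be shifted to a margin, but the margin must then be a hazard ratio. An absolute margin and a hazard ratio coincide at one reference DFS only. If the observed reference DFS is not 88%, the two readings are different standards, and the same data could pass one and fail the other. What is at stake is the trial's main conclusion in an open-label comparison.

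**Working it through.** **Inputs.** From Sample size: 3-year DFS 88% in both arms, margin 8 points, alpha 0.05, power 80%, 20% loss, 361 per group, 40 events per group. Evaluable per arm: 361 × 0.80 = 288.8, taken as 289.

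**1. Reproducing the stated figures.**
- Margin as a hazard ratio: ln(0.80)/ln(0.88) = 0.2231/0.1278 = 1.746, with log 0.557.
- Schoenfeld events at one-sided 0.05: 4 × (1.645 + 0.842)² / 0.557² = 80, which is the stated 40 per group.
- With two-sided 0.05 as written: 4 × (1.960 + 0.842)² / 0.557² gives 102. Freedman's formula gives 84 (one-sided) and 107 (two-sided).
- Patients: 80/(2 × 0.1385) = 289 per arm, and 289/0.80 = 361. The event probability 0.1385 assumes exponential DFS, one year of accrual and three further years of follow-up. The accrual period is an assumption that is not in the article.
- A calculation on the difference scale does not give 361. It gives 260 evaluable per arm (325 with loss) at one-sided 0.025, and 205 (257 with loss) at one-sided 0.05.

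So the sizing appears to rest on an unstated hazard-ratio margin of 1.746.

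**2. How the two margins move apart.** With reference DFS S, hazard ratio 1.746 means S − S^1.746 points, and 8 points means hazard ratio ln(S − 0.08)/ln(S).

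| Reference DFS | HR 1.746 in points | 8 points as HR |
|---|---|---|
| 86% | 9.2 | 1.65 |
| 88% | 8.0 | 1.746 |
| 90% | 6.8 | 1.88 |
| 93% (assumed) | 4.9 | 2.24 |
| 95% (assumed) | 3.6 | 2.72 |

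**3. Can the verdict change?** Two illustrations with assumed results, 289 per arm and events to 3 years.
- *93% observed in both arms.* SE of the difference = √(2 × 0.93 × 0.07/289) = 0.0212, so the lower limit is −1.96 × 0.0212 = −4.2 points, which passes. Events = 2 × 289 × 0.07 ≈ 40, SE of log HR ≈ 2/√40.5 = 0.314, so the upper limit is exp(1.96 × 0.314) ≈ 1.85. That is above 1.746 and fails.
- *89% with biopsy alone against 93%.* HR = ln(0.89)/ln(0.93) = 1.61. Events are about 31.8 and 20.2, SE = √(1/31.8 + 1/20.2) = 0.284, 95% CI about 0.92 to 2.80, so there is no significant difference. On the absolute scale, SE = √((0.89 × 0.11 + 0.93 × 0.07)/289) = 0.0237, and the lower limit is −4 − 1.96 × 2.37 ≈ −8.7 points. The 8-point margin is not met although the log-rank shows nothing.

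The first illustration depends on timing. With 80 events and HR 1, the upper limit would be exp(1.96 × 2/√80) = 1.55, which passes. At 93% DFS only about 40 events would arise by 3 years, when the scheduled visits end.

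**4. Power if DFS is 88% in both arms.**
- Difference scale, 289 per arm, one-sided 0.025: SE = √(2 × 0.88 × 0.12/289) = 0.0270; 0.08/0.0270 − 1.96 ≈ 1.00, so power is about 84%.
- Hazard-ratio scale, 80 events: 0.557 × √80/2 = 2.49. Subtracting 1.96 gives 0.53, power 70%. Subtracting 1.645 gives 0.85, power 80%.

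**The case against.** The best defence has four parts.

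- **The log-rank may already carry the margin.** An unshifted log-rank could not have 80% power with 88% assumed in both arms, and the 80 events reproduce from a test shifted to 1.746. This stands as an account of how the trial was sized. It does not supply a rule, because the bound is not stated and the analysis section repeats the log-rank without it.
- **A 95% interval of the difference is promised.** With Kaplan-Meier estimates and an absolute margin, this is close to what is needed. It would answer the point if it named the 3-year DFS difference and the limit to compare with 8 points. It does neither.
- **Detail may sit in an analysis plan that is not shown.** That is fair for standard-error methods and supportive analyses, and such a plan may fix the scale. So a reader might infer that the analyst will choose the scale after seeing the data, but the article does not show that. The point here is different: the article positively names a test that does not match its margin, in both the analysis and the sample-size sections.
- **The power loss can be exaggerated.** A reader might count only 3-year events (2 × 289 × 0.12 ≈ 69 at 88% DFS) and conclude that hazard-ratio power is 64%, falling further as DFS rises. The article plans 80 events, at which it is 70% or 80% depending on sidedness. The lower figures are not supported.

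A reader might also infer that DFS will exceed 88%, since the Background cites total recurrence of 4.3% and 7.3%. Those rates come without a time horizon, while DFS also counts deaths. The protocol also provides for patients with grade 3 disease, deep invasion or lymph-vascular space invasion. The evidence is weak, so 93% and 95% serve here only as assumed values.

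**Conclusion.** The point holds. Followed as written, the primary comparison is a log-rank test without a margin, and a non-significant result would not establish non-inferiority within 8 points. The hazard ratio behind the sizing, 1.746, is not stated and equals the stated margin only at 88% reference DFS; at 90% it is already a 6.8-point margin.

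The size of the disagreement depends on a DFS level that the article cannot settle, and the illustrations rest on 289 evaluable per arm, events to 3 years and normal approximations. It would be wrong to say that the scales differ only away from 88%: that is true of the margins, but at 88% power already differs (84% against 70% at one-sided 0.025). Nor does this show that 722 patients are too few, since they suffice on the absolute scale. The mismatch between one-sided and two-sided alpha, and the null hypothesis worded as non-inferiority, are separate points.

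**What to change.** State one primary analysis: the difference in Kaplan-Meier 3-year DFS, biopsy alone minus biopsy plus lymphadenectomy, with a two-sided 95% confidence interval. Non-inferiority is concluded if the lower limit is above −8 points. Make the log-rank test and the Cox hazard ratio with its interval supportive, and report beside them the hazard ratio that 8 points implies at the observed reference DFS.

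Stating 1.746 as the bound would also give a coherent rule. It would no longer be the absolute margin that the article states, and at two-sided 0.05 it would need 102 events for 80% power.

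The cost is wording, to be settled before the final data; the article expects the last participant to reach the endpoint in 2028. No patients need adding: 260 evaluable per arm, or 260/0.80 = 325 with loss, are enough at one-sided 0.025, against 361 planned. The downside is that the hazard ratio loses primary status, and the absolute margin is the more lenient scale if DFS is above 88%. That is why the implied hazard ratio should be reported alongside.
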